#### Secondary outcomes

Additional secondary outcomes are presented in Table 2. All secondary outcomes will be compiled at 1, 6 and 12 months after baseline from the same data already collected for the primary outcome, with the exception of self-efficacy as well as action and coping planning which are collected during the ongoing counselling on Likert-type scales with five levels.

**Table 2 Tab2:** Secondary outcomes

Secondary outcome	
Smoking cessation rates in intervention and control groups among patients with *high intrinsic motivation* to stop smoking	
Smoking cessation rates in intervention and control groups among *all* participants	
Reduction in number of cigarettes per day, compared to baseline	
Weight loss in units of 1 kg, compared to baseline	
Increase in physical activity time per week in units of 5 min, compared to baseline	
Reduction in number of standard drinks per week, compared to baseline, and number of alcohol-free days per week	
Reduction in score of the Perceived Stress Scale (PSS-10, German version), compared to baseline	
Increase in score of translated MedDietScore questionnaire, compared to baseline	
Patients’ degrees of motivation and, if applicable, confidence to achieve and maintain a change in behaviour (self-efficacy)	
If applicable: availability of a plan on when and how to take action (action planning) and existence of a relapse plan (coping planning)	

Additionally, the covariates presented in Table 3 are collected, if applicable.

**Table 3 Tab3:** Covariates

Covariate	Source
Biopsychosocial data of general practitioners (age, gender, experience, type of doctor’s practice, data of medical assistants/nurses)	GP
Biopsychosocial data of patients (age, gender, marital status, educational level, smoking status of partner)	Patient
Characterisation of smoking behaviour (age at onset of smoking, pack-years, number of cigarettes per day, time to first cigarette after wake up, number of previous attempts to stop smoking)	Patient
Participants’ choice of behavioural dimension	GP
Number and duration of coaching/counselling sessions (per patient and in total)	GP
Person conducting the coaching/counselling (doctor or specifically trained medical assistant)	GP
Type of smoking cessation intervention used	GP
Dispense of decision aids	GP
Involvement of partner or peers into the coaching/counselling process	GP
Perceived partner or peer support	Patient
Perceived willingness of partner or peers to achieve the same change in behaviour	Patient

*GP* general practitioner

#### Process outcomes

In parallel to the ongoing study, additional data will be collected regarding the implementation, effectiveness and cost–benefit ratio of the intervention with the aim of forming a solid basis for decision about further promotion and dissemination of the Health Coaching programme. The results of the evaluation are expected to lead to more profound insights into the methodology of the intervention, in how to optimally train the multiplicators and into factors influencing the acceptance of the intervention by the target population. Furthermore, the process evaluation comprises an analysis of the costs generated by the intervention.

We chose the RE-AIM framework [16] by Glasgow et al. [17] as a comprehensive concept within which to address these objectives.

Process outcomes (Table 4) will be evaluated based on case report and log files used within the actual trial and also using additional methodology specific to the respective questions: semi-structured interviews, questionnaires, telephone interviews and focus group sessions.

**Table 4 Tab4:** Process outcomes

Process evaluation outcome	Source
Reach: proportion and representativeness of individuals receiving the intervention (individual level)	
Rate of smokers among the GP's patients	GP
Rate of smokers invited to participate	GP
Rate of refusals, with reasons	GP
Patient dropout rate, with reasons	GP
Patients’ characteristics and representativeness	See covariates
Efficacy: success rates of the intervention (including satisfaction outcomes) under study conditions (individual level)	
Behaviour change rates	See outcomes
Changes in self-efficacy and planning	See outcomes
Patients’ current overall satisfaction with coaching programme	Patient
Adoption: proportion and representativeness of organisations willing to adopt the intervention, with consideration of enablers and barriers to adoption (organisational level)	
Rate of GPs invited to participate	SC
Rate of refusals, with reasons	SC
GP dropout rate, with reasons	SC
GPs' characteristics and representativeness	See covariates
Involvement of medical assistants/nurses	See covariates
Assistants'/nurses' characteristics	See covariates
Assessment of GPs' precognitions, understanding of coaching/counselling concept and increase in knowledge and skills, evaluation/rating of coaching/counselling concept and structure of training, recommendation to colleagues	GP
Time required for coaching/counselling	See covariates
Rating of coaching/counselling tools in matters of usefulness and manageability, enabling factors and barriers in coaching/counselling as perceived from practical experience	GP
Overall assessment: benefit for daily practical work, most crucial aspects (success factors and pitfalls), suggestions for improvement, overall satisfaction	GP
Implementation: extent to which the intervention is implemented under real-world conditions—patient adherence (individual level) and adherence of staff to study protocol (organisational level)	
Number of coaching/counselling sessions per patient	See covariates
GPs'/assistants'/nurses' attitudes, competences and (mental) barriers towards/in/to delivering the interventions	GP
Changes in contents or duration of coaching/counselling elements during the ongoing trial	GP
Completeness/integrity of data reported by GPs	SC
Costs arising from expenditure of coaching time	SC
Maintenance: sustainability of intervention over time—relapse rates (individual level) and integration of intervention into institutional routine (organisational level)	
Upholding of beneficial behaviour at 12 months after end of follow up	Patient
Number of GPs trained in HC until 12 months after end of follow up	HC registry
Number/frequency and quality/intensity of coaching over a period of 12 months beyond follow up	GP
Response among experts and media coverage	Experts, media
Maintenance costs	GP

*GP* general practitioner, *HC* Health Coaching programme, *SC* study centre

#### Safety outcomes

Adverse events are defined as any untoward medical occurrences in patients after the intervention and do not necessarily have a causal relationship with study activities. In particular, the following will be considered as adverse events:Complication of an existing disease.Onset of new acute illness.Hospitalisation or death.

Adverse events will have to be recorded by the GPs in the patients’ case report files and reported to the study centre. The study investigators will decide together with the respective GP whether there is a plausible connection between intervention and adverse event.

### Follow up

At 1, 6 and 12 months post baseline the patients will report in mail form about their health behaviour status (regarding smoking, weight, activity, alcohol, diet, stress and—if applicable—self-chosen behaviour dimension). Patients claiming to have achieved tobacco abstinence at 12 months after baseline will also be asked to provide a saliva sample for confirmatory cotinine testing.

In addition to a base compensation, the GPs will be rewarded with financial compensation for every patient providing full follow-up data.

### Sample size calculations

For sample size calculations with respect to the superiority hypothesis, we assume success rates of 40% in the intervention and 15% in the control group. The 40% assumption is based on results from the preceding study [8] in which one out of two participants declared subjective improvements in their self-chosen behavioural dimension after coaching. The success rate of 15% in the control group is the sum of a 10% smoking cessation rate achievable by state-of-the-art smoking cessation counselling according to Comuz et al. [18] plus an estimated 5% of “spontaneous” effects of smoking cessation counselling on one of the other behavioural dimensions. Using *α* = 5% (two-sided) and *β* = 10% we calculated a sample size of 62 participants per equally sized study arm [19] or 2 · 62 / (1 – 0.25) = 166 participating smokers in total after factoring in a dropout rate of 25%. To reflect the correlation structure of the clustered design, an intra-cluster correlation coefficient (ICC) of 4% was assumed, which is slightly higher than corresponding values suggested by Parker et al. [20], in order to account for rare cases of GPs from the same group practice. This assumption is also backed by (unpublished) calculations from the previous study [8] with similar cluster structure and outcome. Correction for the cluster effect increases the sample size to 166 · [1 + (4 – 1) · 0.04] = 186 or roughly 200 patients, assuming that a general practitioner is able to recruit four patients. Finally, allowing for a dropout rate of 15% among general practitioners, 186 / 4 / (1 – 0.15) = 56 (rounded to the next higher even number) or roughly 60 general practitioners must be recruited to detect the expected difference in the primary outcome between the two study arms.

Sample size calculations with respect to the non-inferiority hypothesis require additional assumptions. In the earlier study [8], 12% of smoking or non-smoking GP patients chose smoking cessation as their primary goal. For the present study with smoking participants only, we cautiously assume that in both study arms 25% (i.e. roughly double this number) are highly motivated to give up smoking. Based on Lindson-Hawley et al. [21], we further assume a 40% success rate among the highly motivated. Using a tentative and rather large non-inferiority margin of 10% as in [21] and *β* = 20%, this results in an uncorrected sample size of 297 highly motivated participants per study arm [22] or 2 · 297 / (1 – 0.25) · [1 + (4 – 1) · 0.04] · 4 = 3550 participants in total after correction for clustering and dropouts. Sample size calculations with regard to smoking cessation rates among *all* participants lead to even larger samples, not feasible with available resources. Accordingly, we chose “any relevant behaviour change” as the primary outcome and will consider smoking cessation efficacy among the secondary outcomes.

### Data collection procedures

Patients will receive detailed written information on the aim of the study. After obtaining their written informed consent, data will then be collected by means of paper case report forms (CRFs). For every patient, a dossier with the different CRFs will be created. The forms will be encoded and the codes stored at each GP’s practice. Decoding will be possible if case-tracking is needed (in case of adverse events). Data transfer from paper to electronic form will be carried out and double-checked independently by different research associates.

### Statistical analysis

Baseline characteristics (qualitative and quantitative variables) of GPs and patients will be calculated after recruitment is completed for each arm of the study, with corresponding 95% confidence intervals where applicable.

Crude success rates (i.e. rates of any relevant health-promoting behavioural change and smoking cessation rates) will be compared between intervention and control groups using χ^2^-tests after completion of follow up. As the main analysis, adjustment for cluster effects will then be performed by (multivariate) hierarchical logistic regression with individuals as the unit of analysis, grouping by GP as the random effect and covariates (including the balancing variables) as independent fixed effects.

Changes in outcome measures that do not meet the criteria for clinical relevance defined in Table 1 will be described and presented graphically (density plots, histograms), compared across study arms using χ^2^-tests or *t*-tests and adjusted by random-effects regression models analogous to those used for success rate comparisons, but with the respective behavioural change measures as dependent variables.

All analyses will be conducted following an intention-to-treat (ITT) approach (i.e. outcome data will be obtained from all participants and analysed “as randomised”). Missing values will be replaced by standard multiple imputation (MI) as recommended by Ma et al. [23] for clustered designs with variance inflation factors < 3. Non-responder imputation (NRI; i.e. conservatively treating all missing values as failures) will be used within the scope of sensitivity analyses.

Qualitative information from the process evaluation will be analysed using common coding techniques for qualitative data. A coding tree will be established deductively based on pre-determined domains of interest and refined by inductively adding codes where appropriate. Results will be reported in percentages or categories. Proportions or mean values of different subgroups will be compared using χ^2^-tests or *t*-tests.

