## Abstract

**Background:**

Tobacco abuse is a frequent issue in general practitioners' (GPs') offices, with doctors playing a key role in promoting smoking cessation to their patients. However, not all smokers are ready and willing to give up smoking. Thus, a GP focusing on smoking cessation alone might waste the opportunity to improve his patient’s health by supporting a change in another harmful behaviour pattern. The aim of this study is to determine whether multi-thematic coaching will lead to higher overall health benefits without resulting in a reduced rate of successful smoking cessations, compared with a monothematic smoking cessation approach.

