### Study hypothesis

We hypothesise that multidimensional and patients’ motivation-driven brief interventions by GPs improve several relevant health outcomes of smokers. We assume that these improvements surpass the beneficial effects of monothematic state-of-the-art smoking cessation counselling, and we further assume that the smoking cessation rates achievable through the novel interventions are not inferior to those known from state-of-the-art smoking cessation counselling.

To verify these hypotheses, we plan to train the GPs in the intervention group in how to coach smokers according to the Health Coaching programme [6], while the control group GPs will undergo training in monothematic smoking cessation counselling [5].

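### Non-inferiority of smoking cessation is a stated aim and hypothesis, but cessation is analysed only with methods for a difference, with no margin, at a sample that cannot settle the question

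*Protocol article*

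**What the plan says.** The aim in the Abstract (Background) is higher overall benefit "without resulting in a reduced rate of successful smoking cessations, compared with a monothematic smoking cessation approach". The Study hypothesis section repeats this as a formal assumption: "we further assume that the smoking cessation rates achievable through the novel interventions are not inferior to those known from state-of-the-art smoking cessation counselling". It then treats superiority on the composite and non-inferiority on cessation alike: "To verify these hypotheses, we plan to train the GPs in the intervention group".

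The Sample size calculations section works out a non-inferiority comparison among highly motivated smokers: "Using a tentative and rather large non-inferiority margin of 10" per cent, it arrives at 297 per arm and 3550 participants in total. It adds that a calculation for all participants would need still more, which is not feasible. Cessation is therefore placed among the secondary outcomes. Table 2 lists it twice, for the highly motivated and for everyone.

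The Statistical analysis section assigns the tests: "Crude success rates (i.e. rates of any relevant health-promoting behavioural change and smoking cessation rates) will be compared between intervention and control groups", by chi-squared tests once follow-up is complete. A hierarchical logistic regression with GP as random effect follows as the main analysis. The 10-point margin does not reappear there, and no one-sided level, confidence bound or rule for interpreting the cessation result is given.

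**The concern.** A test of no difference and a test of non-inferiority ask different questions. A non-significant difference test shows only that the data are compatible with no difference. Non-inferiority requires the confidence interval to exclude a loss larger than a margin fixed in advance. The plan has the hypothesis and, in another section, a tentative margin, but the analysis does not connect the two. The regression does not close the gap as written, because its natural scale is the odds ratio and the only margin in the document is a difference in percentage points.

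What is at stake is the conclusion the trial may draw on its second hypothesis. In a sample this small, a non-significant cessation result is the likely outcome even if coaching lowers quit rates substantially.

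**Working it through.** **Inputs from the protocol.** Planned total 200 patients (Patient recruitment and allocation). Patient dropout 25%, ICC 0.04, four patients per GP, control cessation rate 10% among all participants (Sample size calculations, superiority part). Highly motivated share 25% in both arms, cessation 40% among them, margin 10 points, beta 20% (Sample size calculations, non-inferiority part). The alpha for non-inferiority is not stated.

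**Reproducing the plan's figure.** n per arm = 2 × p(1 − p) × (z for alpha + z for power)² / margin².
- One-sided 5%: 2 × 0.24 × (1.645 + 0.842)² / 0.10² = 296.8, so 297, as stated.
- One-sided 2.5% would give 377. The plan therefore appears to use one-sided 5%.
- Total: 2 × 297 / 0.75 × 1.12 × 4 = 3548, stated as 3550.
- The planned 200 are 200 / 3550 = 5.6% of that.

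**Effective sample.** Design effect = 1 + (4 − 1) × 0.04 = 1.12.
- All participants: 200 × 0.75 / 1.12 / 2 = 67.0 per arm.
- Highly motivated: 67.0 × 0.25 = 16.7 per arm.

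**Highly motivated, true rates 40% in both arms.**
- SE of the difference = √(2 × 0.24 / 16.74) = 0.169.
- 95% CI half-width = 1.96 × 0.169 = 0.33.
- Non-inferiority power = Φ(0.10 / 0.169 − 1.645) = 0.146 at one-sided 5%, and Φ(0.10 / 0.169 − 1.96) = 0.085 at one-sided 2.5%.

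**All participants, true rates 10% in both arms.**
- SE = √(2 × 0.09 / 66.96) = 0.052; 95% CI half-width 0.10.
- Power at a 10-point margin would be 61% (one-sided 5%) or 49% (one-sided 2.5%). That margin equals the whole assumed control rate, so meeting it would not rule out the loss of nearly all quitting.
- The plan names no other margin for this group. Its remark that all participants would need an even larger sample must rest on a smaller, unstated one: at 10 points the same formula gives 112 per arm, or 2 × 112 / 0.75 × 1.12 = about 335 in total.

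**What the crude chi-squared test would miss** (exact enumeration, two-sided 5%, effective sizes rounded to 17 and 67; the lower rates are assumptions for illustration).

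| Group | True rates | Power | Missed |
|---|---|---|---|
| Highly motivated | 40% v 30% (loss equal to the margin) | 0.09 | 91% |
| Highly motivated | 40% v 20% (halving) | 0.23 | 77% |
| All participants | 10% v 5% (halving) | 0.20 | 80% |

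**The case against.** The strongest reply is that the protocol is candid. It computes the sample that non-inferiority would need, says it cannot be reached, calls its own margin tentative and rather large, and lists cessation as secondary. It can be added that an interpretation rule for a secondary outcome often sits in an analysis plan, and that none is shown here. This lowers the priority of the point and shows that the authors knew the limit. It does not remove the mismatch: the aim and hypothesis still promise verification, and the article itself names the methods for cessation.

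Three stronger readings are tempting and should not be made.
- A reader might infer that a non-significant test will be reported as cessation not reduced and then used to support dissemination. No section says so. The Process outcomes section ties dissemination to implementation, effectiveness and cost–benefit data, not to a cessation p-value. What can be said is that the plan offers no other rule and does not exclude that reading.
- A reader might take the chi-squared test as the decisive analysis. It is the crude step. The mixed model is the main analysis and could yield a confidence interval, though no margin is set on its scale. The miss rates above describe the crude test only.
- A reader might object to non-responder imputation being described as "conservatively treating all missing values as failures", since treating missing patients as failures can draw the arms together and favour non-inferiority. It is only a sensitivity analysis, with multiple imputation as the main method. The shrinkage also depends on similar missingness in both arms. With an interval of about 33 points either side, no false claim of non-inferiority would follow from it.

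**Conclusion.** The point holds as an inconsistency within the protocol: non-inferiority of cessation is to be verified, but the specified analysis contains nothing that could verify it, and the plan's own calculation shows that the sample could not do so either. Only about one trial in seven (one-sided 5%), or one in twelve (one-sided 2.5%), would show non-inferiority among the highly motivated if the arms were truly equal.

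These figures rest on the protocol's own 25% dropout, ICC of 0.04, four patients per GP, 25% motivated share and 40% and 10% cessation rates, on equal rates in both arms for the power and interval widths, and on normal approximations for both. The inferred one-sided 5% level is what reproduces the plan's 297. Other plausible inputs would shift the numbers but not the direction, given that the planned sample is about 6% of what the plan says is required.

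**What to change.** 1. In Statistical analysis, report for smoking cessation the cluster-adjusted risk difference with its confidence interval, at a stated level. For the highly motivated, read it against the 10-point margin already used in Sample size calculations. For all participants, present it as estimation only, since 10 points equals the whole assumed control rate.
2. State there that a non-significant difference in cessation will not be taken as evidence of non-inferiority.
3. Reword the aim in the Abstract and the Study hypothesis section so that the trial estimates the difference in cessation and is not powered to establish non-inferiority.

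This is a change of wording plus one additional model-based estimate, with no extra patients or data. It cannot restore power: at this sample the reading against the margin will usually be inconclusive. The price is a more modest claim about cessation.

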## Methods/design

### Study design and setting

A cluster randomised controlled trial (randomisation on the GP level) will be conducted with 60 German-speaking GPs from the northern part of Switzerland (see Fig. 1 for the study flow chart). The design and methodology of the study are partly based on experiences gained from a previous trial carried out by the last author in eastern Switzerland [8]. The SPIRIT checklist for this protocol can be found in Additional file 1.

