### Cluster randomisation

Participating GPs will be listed chronologically, and GP characteristics collected prior to their allocation to either intervention or control arm. Until their required number is reached (according to the sample size calculation), the GPs will be allocated to the two equally sized study arms in blocks of 14–20 GPs each, by means of a tailored covariate constrained randomisation procedure [9] with an additional constraining criterion regarding potential contamination. In some more detail, a set of sufficiently balanced allocations with regard to the GPs' sex, contract status and practice type will be constructed and then purged from contamination-prone allocations (i.e. from those which put GPs belonging to the same group practice into different study arms), before randomly drawing the final allocation to be used in the study. All GPs from the same group practice will be allocated within the same block.

The block size was chosen to meet recommendations by Carter and Hood [10] and also with a view to training group sizes that can well be handled within the study centre’s resources. To generate the set of balanced allocations, we will use the web-based Shiny Balancer [11], and the additional reduction step will be carried out manually using Excel’s sorting and filtering capabilities. The final random draw will be carried out by a study nurse not involved in the later data analysis.

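### Group practices are allocated intact to one arm, but the main model clusters by GP only, so the primary standard error is too small to the extent that GPs share a practice

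*Protocol article*

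**What the plan says.** All of this is in the Methods/design part of the protocol article.

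- **Study design and setting** names the GP as the unit: "A cluster randomised controlled trial (randomisation on the GP level) will be conducted with 60 German-speaking GPs".
- **Cluster randomisation** first builds a list of allocations balanced on GP sex, contract status and practice type. It then removes from that list the allocations "from those which put GPs belonging to the same group practice into different study arms", and only afterwards makes the random draw. It adds: "All GPs from the same group practice will be allocated within the same block". On blocks it says: "the GPs will be allocated to the two equally sized study arms in blocks of 14–20 GPs each".
- **Sample size calculations** sets the ICC at 4%, slightly above the cited values, "in order to account for rare cases of GPs from the same group practice".
- **Statistical analysis** defines the main analysis as a hierarchical logistic regression on individual patients, "grouping by GP as the random effect", with covariates that include the balancing variables as fixed effects. Models of the same kind are used for the individual behaviour changes. Neither the practice nor the allocation block is named.

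**The concern.** Two GPs in the same practice can never be drawn into different arms. For them the practice, not the GP, is the unit of allocation. A model with a GP random effect allows for similarity among one GP's patients but assumes that patients of two partner GPs are independent. If partners' patients are positively correlated, the treatment comparison carries practice-level variation that the model does not count. The standard error is then too small, the confidence interval too narrow and the type I error above the planned 5%.

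The planning section recognises shared practices, but a higher planning ICC only buys patients. At analysis, the variance comes from the fitted model. Adjusting for practice type does not replace a practice term, because it is a category and does not identify which GPs work together.

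The blocks raise a separate question. Allocation is done block by block, so a model that follows the design would carry block. The possible loss here is precision, not validity.

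**Working it through.** **Inputs from the article (Sample size calculations):** success 40% versus 15%, two-sided alpha 5%, power 90%, patient dropout 25%, ICC 0.04, m = 4 patients per GP, GP dropout 15%.

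**The article's own figures, reproduced**

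- Per arm, unpooled variance: (1.960 + 1.282)² × (0.40 × 0.60 + 0.15 × 0.85) / 0.25² = 61.8, so 62.
- Patient dropout: 2 × 62 / 0.75 = 165.3, so 166.
- Clustering: 1 + (4 − 1) × 0.04 = 1.12, and 166 × 1.12 = 185.9, so 186.
- GPs: 186 / 4 / 0.85 = 54.7, so 56 as the next even number.

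The design effect of 1.12 is the one that a GP-only analysis accounts for.

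**Adding the practice level**

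Three quantities are not in the article and are assumptions: s, the share of GPs in a shared practice; k, the number of trial GPs in such a practice; and ICC_p, the correlation between patients of different GPs in one practice.

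- Design effect: DE = 1.12 + s × (k − 1) × m × ICC_p.
- Model SE over true SE: √(1.12 / DE).
- Actual type I error: 2 × [1 − Φ(1.96 × √(1.12 / DE))].

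Example with s = 0.5, k = 3, ICC_p = 0.04: DE = 1.12 + 0.5 × 2 × 4 × 0.04 = 1.28; √(1.12 / 1.28) = 0.935; 1.96 × 0.935 = 1.833; type I error 6.7%.

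| s | k | ICC_p | DE | SE ratio | Type I error | Patients, 166 × DE |
|---|---|---|---|---|---|---|
| 10% | 2 | 0.01 | 1.124 | 0.998 | 5.0% | 187 |
| 10% | 3 | 0.04 | 1.152 | 0.986 | 5.3% | 192 |
| 25% | 2 | 0.02 | 1.140 | 0.991 | 5.2% | 190 |
| 20% | 3 | 0.04 | 1.184 | 0.973 | 5.7% | 197 |
| 50% | 3 | 0.04 | 1.280 | 0.935 | 6.7% | 213 |
| 100% | 4 | 0.04 | 1.600 | 0.837 | 10.1% | 266 |

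Ten per cent of 60 GPs is six GPs, that is, three practices of two or two of three. The last row is an extreme that the article does not expect. With m = 3 analysed patients per GP (4 × 0.75), the 50% row becomes DE = 1.20 against 1.08, SE ratio 0.949 and type I error 6.3%.

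**Leaving out block**

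Blocks of 14 to 20 among 56 to 60 GPs give about three or four blocks. The effect was simulated on GP means on a linear scale: four blocks of 14 GPs split 7:7, three patients per GP, ICC 0.04, no shared practices, 20,000 runs per setting. The within-block variance of a patient's outcome is set to 1.

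| Between-block variance | Model SE / true SE, block omitted | Type I error, omitted | Type I error, included |
|---|---|---|---|
| 0 | 1.00 | 4.8% | 4.8% |
| 0.02 | 1.02 | 4.4% | 4.8% |
| 0.04 | 1.04 | 4.1% | 5.0% |
| 0.08 | 1.08 | 3.5% | 4.9% |

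Because the arms are balanced within each block, the estimate itself does not change. Only its stated standard error grows when block is left out.

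**The case against.** The strongest reply is that the article has already judged the matter small. It states GP-level randomisation, calls shared practices rare, and raises the ICC for them. For a solo GP, the GP random effect is exactly right. On the article's own expectation the standard error is too small by roughly 0.2 to 1.4%, which is unlikely to change the conclusion if the true contrast is near 40% versus 15%. Taking the full 0.04 between patients of different GPs is also severe: it makes partners' patients as alike as one GP's own. The article says trained assistants may deliver sessions, but not that they serve several GPs.

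Most of this stands as a limit on size. It does not remove the mismatch. Rarity is an expectation, since the eligibility section sets no limit on GPs per practice, and the ICC allowance does not reach the fitted model.

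On block, the reply goes further. The covariate list is open-ended, and a full analysis plan may add block. A reader might infer that leaving out block also makes standard errors too small. The documents do not support that: arms are of equal size within blocks, so the omission is neutral or conservative.

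Nesting GP within practice would also be a poor remedy. With three or four patients per GP and few shared practices, the practice variance would be barely identifiable and could well be estimated as zero.

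**Conclusion.** The point holds for GPs who share a practice. They are allocated together, the main model treats them as independent, and the standard error of the primary effect is too small whenever practice-level correlation is above zero. The same applies to the analogous secondary models.

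The likely size is small: type I error about 5.0 to 5.3% if around 10% of GPs share practices of two or three with a practice-level ICC of 0.01 to 0.04. It reaches about 6.7% only if half the GPs are in practices of three with ICC 0.04. These shares, practice sizes and practice-level ICCs are all assumptions.

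Two stronger readings go too far. One is that the practice is the randomised unit throughout, which is not so for solo GPs. The other is that standard errors are understated by factors such as 1.07, 1.13 or 1.25. Those are √(1.28/1.12), √(1.44/1.12) and √(1.76/1.12), and they describe a trial made up entirely of practices of two, three or five GPs, which the article's wording on rarity rules out. The sample size is not materially at fault either: the rounded target of 200 covers a design effect up to 200/166 = 1.20.

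Not naming block is a matter of efficiency. It costs precision only if success differs between blocks.

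**What to change.** In the main model and the analogous secondary models:

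- group the random effect by practice, with a solo GP counted as a practice of one, instead of by GP;
- add allocation block as a fixed effect alongside the balancing variables.

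It would also help to report how many GPs shared a practice, so that readers can see how much the change matters.

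The cost is low. Practice membership and block must be known to carry out the allocation, so no new data are needed. Intervals become slightly wider where practices are shared and hardly change if few are. Block uses two or three degrees of freedom with three or four blocks. A practice-only random effect gives partners' patients the same correlation as one GP's own patients, a simplification that is acceptable with so few patients per GP.
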